**Discussion:**

This study aims to provide confirmatory evidence of the effect of the Korean herbal medicine, KGT, on improving cognitive function in patients with aMCI. We will identify the possible mechanisms underlying the effects of KGT using neuroimaging signals and blood biomarkers.

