### Outcome

The primary outcome includes changes in cognitive performance after the administration of KGT or placebo granules. SNSB, which is composed of various cognitive tests such as CDR, GDS, and MMSE will be conducted to assess the cognitive function, and changes in SNSB results will be analyzed. The secondary outcomes include the rate of progression to AD at the endpoint, according to NINCDS-ADRDA and CDR-GS score ≥ 1. In addition, we will measure neuroimaging signals and blood-based biomarkers. Structural MRI and functional MRI (fMRI) will be adopted to observe neuroimaging signal changes. The changes in gray matter volume will be measured using structural MRI. Also, Rs-fMRI and task-based fMRI will be performed to compare the changes in functional connectivity among working memory and default mode networks and to measure the changes in brain activation during the face–name association task and one-back working memory task. Levels of plasma Aβ42 and Aβ40 will be measured as blood-based biomarkers. The safety outcomes include electrocardiogram (ECG) and blood chemistry (Na, K, Cl, AST, ALT, BUN, Cr, glucose, LDH, CPK).

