#### Data analyses

An independent professional statistician, who will also be blinded to the allocation, will perform data analyses using SPSS 20.0 software (IBM, Armonk, NY, USA). Efficacy analyses will be performed using the modified intention-to-treat (mITT) and per-protocol (PP) principles. The mITT population will include participants who have completed at least one examination since the beginning of the intervention. The PP population will include participants who will adhere to the trial protocol and undergo all examinations. Missing data will be adjusted using the last-observation-carried-forward (LOCF) imputation method. A safety test will be performed using the ITT principle. The ITT population will include any participants who will take at least one pack of drugs after randomization. To analyze the efficacy outcome and continuous demographic variables, we will perform the Shapiro-Wilk test to confirm the normality of the data distribution. To analyze the fMRI measures and plasma amyloid beta levels, the paired *t*-test will be used for intra-group comparisons and an independent *t*-test will be used for intergroup comparisons, for normally distributed data. Wilcoxon’s signed rank test will be used for intra-group comparisons and the Mann-Whitney U test for intergroup comparisons of non-normally distributed data. To analyze the scores of the neuropsychological test battery, repeated measures of analysis of variance will be used for parametric data, and the Friedman test for non-parametric data. Categorical demographic variables, conversion to normal cognition or dementia, conversion to positive plasma Aβ42/Aβ40 ratio (< 0.1218), and the incidence of AEs between the groups will be analyzed using the Pearson’s chi-square (χ^2^) test or Fisher’s exact test. Continuous demographic variables will be analyzed using the *t*-test or Wilcoxon signed-rank test. All statistical analyses will be two-tailed, and the significance level will be set at *p* < 0.05.

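### The fMRI and plasma amyloid measures are tested both within and between arms at p < 0.05, and the plan does not say which test supports a conclusion about KGT

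*Protocol article*

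**What the plan says.** Under Data analyses, the protocol article assigns the tests: "To analyze the fMRI measures and plasma amyloid beta levels, the paired *t*-test will be used for intra-group comparisons". To compare the arms it plans an unpaired t-test on the same measures. If the data are not normal, the signed-rank and Mann-Whitney tests replace them. The section closes with one general rule: "All statistical analyses will be two-tailed, and the significance level will be set at" p < 0.05. It names no leading imaging contrast and does not rank the within-arm and between-arm tests.

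The Outcome section lists the imaging targets. On structural MRI it says: "The changes in gray matter volume will be measured using structural MRI". Resting-state fMRI is to be used "to compare the changes in functional connectivity among working memory and default mode networks", and task-based fMRI measures activation in a face–name task and a one-back task. The MRI section places scans at baseline and week 24. The sentence that assigns the tests covers fMRI and plasma amyloid only, so gray matter volume falls under the general 0.05 rule alone.

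On use, the Discussion paragraph of the Abstract says: "We will identify the possible mechanisms underlying the effects of KGT using neuroimaging signals and blood biomarkers". The main Discussion, in its paragraph on multimodal MRI, likewise expects imaging to help explain the neural basis of the KGT effect.

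**The concern.** There are two linked weaknesses.

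First, a paired test in the KGT arm asks whether that arm changed, not whether KGT changed it. Anything that moves both arms alike, such as a retest effect, the passage of time or regression to the mean, can make it significant. With a paired test in each arm, a result of significant under KGT and not under placebo is easily read as a drug effect, although it does not compare the arms.

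Second, several imaging measures, each tested up to three times at 0.05, give a chance of at least one false positive well above 5%.

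What is at stake is the mechanistic part of the report. A chance or retest finding could be presented as how KGT works.

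**Working it through.** **Inputs from the protocol article.** Alpha 0.05, two-sided (Data analyses). Named imaging measures (Outcome): gray matter volume 1, resting-state networks 2, tasks 2, so five in all and four for fMRI only. Each has one change, baseline to week 24 (MRI). Expected evaluable patients: 33 per arm (Sample size calculation).

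**Assumptions.** One summary value per measure, no true effect, and correlation between measures of 0 to 0.5. The plasma ratio is not counted. The article states no familywise error rate and no count of tests, so there is no figure of its own to reproduce on this point. Its sample size does reproduce: d = 0.70 with 80% power gives 33 per arm, and 33/0.8 = 41.25 rounds up to 42.

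**Between-arm tests only.** With k independent tests, the chance of at least one p < 0.05 is 1 − 0.95^k.
- k = 4: 1 − 0.95^4 = 18.6%
- k = 5: 1 − 0.95^5 = 22.6%
- k = 5 with correlation 0.5 between measures, by simulation: about 19%

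**All three tests per measure.** The between-arm test uses the same change scores as the two paired tests, so the three are dependent. A simulation of 20,000 trials with 33 per arm and no effect, keeping that dependence, gave the following.

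| Measures | Correlation 0 | Correlation 0.3 | Correlation 0.5 |
|---|---|---|---|
| 4 (fMRI only) | 38.8% | 36.3% | 33.2% |
| 5 (with gray matter) | 45.7% | 43.1% | 38.2% |
| 10 (assumed) | 70.8% | 64.2% | 55.4% |
| 20 (assumed) | 91.5% | 84.2% | 72.1% |

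The last two rows show how the risk grows if each network or task yields several regions or connections. The article gives no such number.

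**Within-arm tests when both arms shift equally.** The chance that a paired test in one arm of 33 reaches p < 0.05, for a shared shift in SD units of the change score:
- 0.2 SD: 20%
- 0.3 SD: 39%
- 0.4 SD: 61%

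At 0.3 SD, with independent arms, the chance of significant under KGT and not under placebo is 0.387 × (1 − 0.387) = 24%, with no drug effect.

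The pilot figures under Sample size calculation show that such shifts are plausible. The placebo arm gained 8.36 points on the SNSB-D. The implied SD is (22.47 − 8.36)/0.70 = 20.2, so the placebo shift is 8.36/20.2 = 0.41 SD. A paired test in 33 patients would call that significant about 64% of the time. This is a cognitive score, so it illustrates the problem rather than estimating it for fMRI. The fMRI tasks are, however, also memory tasks done twice.

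**What baseline adjustment adds.** If SDs are equal at both visits and r is the baseline to week-24 correlation, a change score has variance 2σ²(1 − r) and the baseline-adjusted value has σ²(1 − r²). The ratio of adjusted to change-score variance is (1 + r)/2, for example 0.75 at r = 0.5 and 0.85 at r = 0.7 (assumed values). Adjustment therefore also gains precision over an unadjusted t-test on changes.

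**The case against.** The strongest defence has four parts.

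1. This is a condensed article. A 0.05 level can apply equally to corrected p-values, and image-level correction is commonly left to the analysis plan. This stands: the text does not say that the tests are uncorrected, and the absence of a correction method is not itself the fault.

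2. A reader might infer voxel-by-voxel testing from the acquisition grid and conclude that false findings are close to guaranteed. The documents do not support that. No section mentions voxelwise maps. Analysis in SPSS, with t or rank tests chosen by normality, suggests one summary value per participant. A 95% chance of a false positive would need about 59 independent tests, a number the article does not give. Multiplying 15 tests out as independent (1 − 0.95^15 = 54%) also overstates the risk, because the three tests on each measure share data.

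3. A between-arm test is planned, and nothing says that drug effects will be inferred from within-arm results. This is true, but nothing says that they will not be. Both kinds of test have the same standing.

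4. Imaging is secondary, the claim concerns possible mechanisms, and the Discussion concedes that fMRI is not yet a reliable marker. This limits the consequence. It does not remove the ambiguity, since the imaging outcomes are not labelled exploratory in a trial described as confirmatory.

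**Conclusion.** The point holds in a limited form. The article fixes within-arm and unadjusted between-arm tests at the same 0.05 level for fMRI and plasma amyloid, and does not say which one carries the conclusion. With one summary for each of the five named imaging measures, the chance of at least one false positive is about 19–23% between arms and about 38–46% if within-arm tests also count. For the four fMRI measures alone, the latter is about 33–39%. These figures assume no true effect, 33 per arm and correlations of 0 to 0.5. They rise with the unstated number of regions or connections.

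The within-arm weakness needs no multiplicity argument, because a shift shared by both arms is enough. The type I error of the primary outcome is not affected.

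**What to change.** Amend Data analyses to state three things.

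1. Conclusions on imaging and plasma biomarkers rest only on the between-arm comparison of week-24 values adjusted for baseline, by ANCOVA or a rank-based version where normality fails.
2. Within-arm tests are descriptive and do not support statements about a drug effect.
3. Imaging findings are exploratory unless they survive Holm or FDR adjustment across the named networks and tasks.

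The first two matter most. The third is partly a matter of preference for secondary outcomes, and its detail can sit in the analysis plan.

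The baseline values are already collected, so no new data, visits or patients are needed. The cost is a few sentences and, in the report, fewer nominally significant imaging results.

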## Discussion

This trial was designed based on our previous pilot study. To the best of our knowledge, it is the first confirmatory randomized clinical trial to evaluate the effect of KGT on cognitive function in aMCI patients.

We examined the feasibility of the trial process and the acceptability of KGT treatment in our previous study. Since the results showed a significant improvement in the CDR-SB score in the KGT group, the same neuropsychological test battery, including CDR, was selected as the primary outcome. Moreover, we observed high adherence and drug compliance, with 10% dropout rate. No serious safety concerns were reported.

Several improvements were considered in the planning of the current trial. First, as with most pilot studies, the relatively small sample size limited the statistical power and generalizability. Therefore, we will include a larger sample size in this trial, as calculated based on the results of our pilot trial. Second, there was no follow-up examination of cognitive function after completing the intervention in our previous trial, so the long-term effects of KGT could not be examined. Therefore, we will conduct a follow-up neuropsychological test 12 weeks after completing the treatment and observe any occurrence of AEs for 12 weeks after the treatment, compared to 4 weeks of post-intervention monitoring in the prior study.

The advantages of this trial include using extensive assessment tools to evaluate the outcomes. First, as in the pilot study, we will use SNSB, which is the full neuropsychological battery, which is composed of comprehensive and diverse cognitive tests, in order to sensitively capture the changes in cognitive function [13]. This is because the instruments frequently used in previous studies, such as MMSE and Alzheimer’s Disease Assessment Scale-Cognitive subscale, lack sensitivity in detecting mild degrees of cognitive decline, which lead to ceiling effects [18].

Next, we will perform multimodal MRI scans in this study, including structural MRI and resting-state and task-evoked functional MRIs. Structural MRI scan of brain atrophy are the most widely accepted markers of AD progression [19]. A decline in hippocampal volume has consistently been related to memory loss in the AD continuum [20]. Since fMRI, which is an indirect measure of brain activity, is useful in the detecting early alterations in brain function, it might be valuable for evaluating the physiological changes over a short time interval [21]. We will investigate the effects of KGT on brain function using both task-based and task-free (resting-state) approaches. Rs-fMRI studies have shown that the progression of memory decline in aMCI is associated with a decline in functional connectivity in DMN regions, which include brain regions related to cognitive function, such as the hippocampus and medial frontal lobe [22]. For task-based fMRI, we will adopt two types of memory paradigms: the face–name association task and the one-back working memory task. By employing cognitive tasks, the fMRI measure will provide information on the changes in brain activity while performing specific activities that mimic the actual difficulties occurring in daily life [21]. Various neuroimaging modalities will be helpful for evaluating the neural underpinning of the effect of KGT.

We will also observe changes in blood-based neuropathological biomarkers, including the plasma levels of Aβ42, which are proposed to reflect the AD pathology and associated neurodegeneration [15–17]. Plasma Aβ levels are correlated with the cerebrospinal fluid (CSF) Aβ levels and Aβ deposition in the brain [23]. Low plasma Aβ42/40 ratios are associated with an increased risk of dementia [24] and greater cognitive decline [25]. We will investigate whether KGT shows any disease-modifying effect via the plasma Aβ42/40 ratio, instead of using CSF biomarkers, which is a costly and invasive process. In addition, plasma Aβ protein levels may provide information about the etiology of MCI.

Despite the strengths of our study, there are some limitations to our protocol. Although we plan to conduct follow-up examinations at the 36th week, the treatment and follow-up periods are relatively short considering the nature of the disease, which is inevitable due to the limited study period. Nevertheless, the 24-week intervention indicated an improvement in cognitive function in our pilot study, and this issue could be resolved by incorporating fMRI measures that can help detect even subtle changes over a short period of treatment. Next, the signals that will be used in this trial, especially fMRI, do not yet provide a reliable AD biomarker or tracking tool due to inconsistent findings of previous studies. However, we anticipate that using a combination of multimodal MRI scans, blood biomarkers, and extensive neuropsychological tests may aid in the better understanding of the effects of treatment.

In summary, the findings of this trial will provide confirmatory evidence for the therapeutic effects of KGT in patients with aMCI. This study will also give insights into the mechanisms underlying the effects of KGT via various biomarkers.

## Trial status

This study began patient recruitment on February 4th, 2022.

## Data Availability

Not applicable.

## Abbreviations

aMCI: Amnestic mild cognitive impairment
AD: Alzheimer’s disease
KGT: Kami Guibi-tang
SNSB: Seoul Neuropsychological Screening Battery
MRI: Magnetic resonance imaging
rs-fMRI: Resting-state functional MRI
Aβ: Amyloid-β
ECG: Electrocardiogram
MMSE: Mini-Mental State Examination
CDR-SB: Clinical Dementia Rating-Sum of Boxes
GDS: Global Deterioration Scale
CDR: Clinical Dementia Rating
K-MMSE: Korean Version of Mini-Mental State Examination
NINCDS-ADRDA: National Institute of Neurological and Communicative Disorders and Stroke-Alzheimer’s Disease and Related Disorders Association
NINDS-AIREN: National Institute of Neurological Disorders and Stroke-Association Internationale pour la Recherche et l’Enseignement en Neurosciences
AST: Aspartate aminotransferase
ALT: Alanine aminotransferase
Cr: Creatinine
KDSQ: Korean Dementia Screening Questionnaire
SAE: Serious adverse event
GMP: Good Manufacturing Practice
CRF: Case record form
CDR-GS: Clinical Dementia Rating-Global Score
fMRI: Functional MRI
BUN: Blood urea nitrogen
Na: Sodium
K: Potassium
Cl: Chloride
LDH: Lactate dehydrogenase
CPK: Creatine phosphokinase
BADL: Barthel-Activities of Daily Living
SGDS: Short-form Geriatric Depression Scale
SNSB-D: SNSB for dementia
GCF: Global cognitive function
BOLD: Blood oxygenation level-dependent
EPI: Echo-planar imaging
T_R_: Repetition time
T_E_: Echo time
FA: Flip angle
FOV: Field of view
3D T1W: Structural 3D T1-weighted
MPRAGE: Magnetization-prepared rapid acquisition of the gradient echo
CBC D/C: Complete blood count & differential count
HDL: High-density lipoprotein
LDL: Low-density lipoprotein
TG: Triglyceride
TFT: Thyroid Function Test
VDRL: Venereal Disease Research Laboratory
AE: Adverse event
IRB: Institutional review board
mITT: Modified intention-to-treat
PP: Per-protocol
LOCF: Last-observation-carried-forward
ITT: Intention-to-treat
ADAS-cog: Alzheimer’s Disease Assessment Scale-Cognitive subscale
CSF: Cerebrospinal fluid
